### Plans to give access to the full protocol, participant-level data and statistical code {31c}

The full protocol, participant-level data and statistical code will be made available upon publication of the primary analysis as supplementary material. These will also be deposited in a data repository for future use.

## Oversight and monitoring

### Composition of the coordinating centre and trial steering committee {5d}

The coordinating centre will be in Hyderabad at the George Institute for Global Health. The Steering Committee comprises Indian and international experts in clinical trials, maternal health, health systems, implementation science and digital health. The trial Steering Committee will meet virtually or in person every 6 months to review trial progress, and be informed of severe adverse events, quality monitoring updates, modifications to the trial protocol, requests for data from other groups and plans for publications and dissemination.

The trial operations group will meet fortnightly (or more often if required) throughout the trial to ensure smooth day-to-day running and recruitment progress and provide organizational support to the field teams. The operations group comprises the project manager, the research staff directly involved and the Principal Investigators from the UK and India. The project manager will meet virtually or in person with each site manager weekly. The site managers have oversight responsibility for the field supervisors in their state.

### Composition of the data monitoring committee, its role and reporting structure {21a}

Given the pragmatic nature of this study and that there will not be an interim analysis, there will not be a data monitoring committee.

### Adverse event reporting and harms {22}

As the intervention aims to support the delivery of guideline-based antenatal and postnatal care already recommended in this setting, adverse events related to the intervention are not anticipated. That said, there may be unintended adverse effects from improved diagnosis of high-risk conditions (e.g. stigma), which could have physical or emotional consequences. All efforts will be taken by the study team to minimise potential harm. The project manager and field supervisors will identify and report any adverse events during the trial and promptly escalate these to the Principal Investigator ([name]). [name] will have the final say on whether such events are categorised as an adverse event (AE) or severe adverse event (SAE). She will be responsible for reporting any SAEs to the study sponsor and ensuring any actions are taken in the mandated timeframe. At the Steering Committee meetings, all adverse events will be reviewed. AEs and SAEs will be transparently reported in the primary publication, the final report to the REC and the final report to the study sponsor (The George Institute for Global Health, India).

### Frequency and plans for auditing trial conduct {23}

Trial conduct will be audited by the Data Management team at the George Institute at the start of recruitment and every 6 months, independently of the operational team. We will report annually to the study sponsor.

### Plans for communicating important protocol amendments to relevant parties (e.g. trial participants, ethical committees) {25}

Any protocol modifications will be reported to the George Institute India and Oxtrec ethics committees for minor or major amendment approval. Once approved, changes will be notified by the project manager to the site managers and field teams, who will inform the relevant health workers and participants. The trial register will be updated with any protocol amendments.

### Dissemination plans {31a}

The trial results will be communicated to the scientific and clinical communities through journal publications, and presentations at international and national conferences. Results will be communicated to local collaborators through written information and education sessions at the study end. Results will be shared with communities and women through local media and events.

## Discussion

This study will test the effectiveness and implementation of a community-based high-risk pregnancy screening and referral programme up to 1 year after birth. In rural India, as in many settings, women must attend antenatal appointments in a clinic or hospital to detect high-risk conditions. We hope to demonstrate that screening by community health workers in the woman’s village or home can be a practical approach to improving the detection of women with high-risk conditions, timely referral and evidence-based management. Uniquely, our intervention considers the impact of conditions detected during pregnancy on women’s longer-term health, with repeated assessments during the first year after birth. We hope to demonstrate that this is a practical approach to implement effective interventions for reducing the endemic problem of anaemia amongst women in India and engaging women who develop GDM or HDP with postnatal screening for diabetes and hypertension. In particular, the mixed quantitative and qualitative data collection in this hybrid effectiveness implementation study will help us analyse implementation outcomes and identify implementation strategies which are context-sensitive and can address implementation barriers of the programme.

The SMARThealth Pregnancy intervention aims to support government efforts to reduce anaemia rates through improved understanding by ASHAs and capacity to perform point-of-care haemoglobin testing. This is in keeping with AMB recommendations.

Our study has several strengths. The pragmatic nature of the trial will generate evidence of the effectiveness of strategies to improve the care of women at high risk of postnatal anaemia, type 2 diabetes or hypertension. Community follow-up after a pregnancy affected by these conditions is not routinely performed in rural India, which misses critical opportunities for prevention.

Our study will be conducted in two states with very different socio-cultural environments, which will improve the generalisability of our findings to other states in India. We are conducting this study as a hybrid effectiveness-implementation design. A separate protocol will be published on the planned implementation outcomes that we will capture through a detailed process evaluation. The analysis of implementation outcomes and strategies will inform the iterative development and steps needed for the eventual scale-up and adoption of the intervention more widely; alternatively, it will explain the factors that contributed to a null trial. As part of the process analysis, we will continue refining our logic model and assumptions regarding how the intervention works and the barriers to implementation, as well as the economic benefits and implications.

We acknowledge our study design has limitations. Owing to funding constraints, we can only involve community health workers from two villages affiliated with each PHC. Thus, the intervention will not be at the population level which might affect primary care physician engagement. We will explore this in detail in our process analysis. The nature of the trial design means there could be benefits above usual care in the control clusters. Participants in both study arms will have their haemoglobin tested and their blood pressure measured at the study visits. Ideally, after a high-risk pregnancy condition, follow-up would extend for life, which is clearly impractical and prohibitively expensive in the context of this study. We believe demonstrating engagement beyond 6 weeks after birth will be a strength. The nature of the complex intervention means that blinding of participants is not practical or feasible, increasing the likelihood of information bias. To minimise this, we will ensure that the trial statistician and investigator group remain blinded to allocation until the primary analysis has been performed.

Given the longitudinal nature of recruitment, not all potential participants will be pregnant before the study starts; therefore, randomisation must occur before participants are recruited. This could bias recruitment, as community health workers will know their allocation group when approaching pregnant women. However, in our pilot study, this was not the case: we achieved equal recruitment and retention rates across both groups.

In summary, we present a study protocol for a pragmatic, cluster randomised hybrid effectiveness-implementation trial to test the SMARThealth Pregnancy complex intervention in rural India. It is hoped that the trial will demonstrate the effectiveness of the intervention and implementation in reducing anaemia and improving, during and after pregnancy, the detection and follow-up of other high-risk pregnancy conditions.

## Trial status

The current protocol number is version 2.0, November 2022. The SMARThealth Pregnancy trial is currently recruiting. Recruitment commenced on 1 July 2022, and the trial is anticipated to run until 30 June 2024.

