**Trial registration:**

ClinicalTrials.gov NCT05752955. Date of registration 3 March 2023.

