#### Eligibility for women

Up to 5000 pregnant women will be screened until the sample size has been reached. Potentially eligible women will be identified by ANMs and ASHAs with the support of laboratory technicians. Women will be eligible if they are ≥ 18 years old. Women can be enrolled at any time during the pregnancy at or after 12 weeks of gestation, as determined by ultrasound scan, date of last menstrual period or best clinical estimate.

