### Outcomes {12}

#### Primary outcome

The primary outcome will be the difference in the proportion of participants with anaemia, defined as haemoglobin measured using a point-of-care test < 12 g/dL at 12 months after delivery between the intervention and EUC clusters. Anaemia has been chosen as the primary outcome as it is the most common condition affecting women during pregnancy and breastfeeding across India. Measurement using a point-of-care device was chosen as this has been recommended in national guidelines and is a common method for diagnosing anaemia in rural settings, thereby reflecting real-world practice. The measurement will be performed by a member of the study team.

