### Participant timeline {13}

PHCs will be recruited and randomised before individual participant recruitment commences. After randomisation, ASHAs in the intervention clusters will attend the education programme to receive training on the clinical conditions, use of the point-of-care devices and SMARThealth Pregnancy app. Individual participants will be approached by their ASHA worker to participate after 12 weeks’ gestation. If they consent to participate in the study, a study team member will complete a baseline assessment, which includes questionnaires, blood pressure and haemoglobin measurement. A study team member will perform a mid-point assessment between 9 and 12 weeks after birth to capture events and healthcare utilisation including out-of-pocket costs around the time of birth. A study team member will conduct the final study visit 9–12 months after delivery, which will involve completing questionnaires, and measuring haemoglobin and blood pressure (Table 2).

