## Statistical methods

### Statistical methods for primary and secondary outcomes {20a}

The primary analysis will be by intention to treat conducted at the participant level, using either random-effects models or generalised estimating equations adjusted for PHC clustering. We used a matched-pair design to balance cluster characteristics prior to randomisation, as recommended for community-based trials with a limited number of clusters [40]. Given the relatively small number of clusters, the analysis will not adjust for matching since this has been shown to provide unbiased estimates of the randomised intervention effect [41] and provide similar power to a matched analysis [40]. An unmatched analysis has the advantage that it can easily be conducted using participant-level data whilst allowing estimation of the intra-class correlation coefficient.

The final analysis is anticipated to occur 36 months after recruitment of the first participant. For the groups to be declared significantly different, the *P* value for the primary outcome must be ≤ 0.05. We will report the point estimate and confidence interval and present an assessment of the clinical relevance of our findings.

Baseline data will be presented for both groups. Continuous variables will be assessed for distribution, with appropriate statistical transformation (e.g. log or cubic splines) to correct for non-normality. Subgroup analyses will be performed by study location (Telangana or Haryana) to explore the effects of contextual factors on outcomes of interest. A detailed statistical analysis plan will be developed and publicly available before unblinding.

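### The stated trial end of 30 June 2024 is too early for the 12-month primary outcome and does not fit the month-36 analysis, and the outcome is measured only at a 9–12 month visit

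*Protocol article*

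**What the plan says.** All references are to the Protocol article.

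- **Trial status:** "Recruitment commenced on 1 July 2022, and the trial is anticipated to run until 30 June 2024". The same paragraph says: "The SMARThealth Pregnancy trial is currently recruiting". That statement carries no date of its own. The article cites its registration ("Date of registration 3 March 2023") and was published on 9 August 2023, so the statement lies between those two dates.
- **Eligibility for women:** "Women can be enrolled at any time during the pregnancy at or after 12 weeks of gestation".
- **Primary outcome:** anaemia is compared "at 12 months after delivery between the intervention and EUC clusters". The Effectiveness row of Table 1 gives the same time point.
- **Participant timeline {13}:** "A study team member will conduct the final study visit 9–12 months after delivery". The footnote to Table 2 (T7) and the outcome collection section {18a} give the same window. Section {18a} lists three data collection occasions, of which this is the only one at endline.
- **Statistical methods {20a}:** "The final analysis is anticipated to occur 36 months after recruitment of the first participant".
- **Missing data {20c}:** the primary analysis population consists of women with a recorded endline haemoglobin.

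**The concern.** Two statements about time do not fit the primary outcome.

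The first is the calendar. A 24-month trial has to hold the recruitment period, the rest of each pregnancy and up to a year of follow-up. Recruitment was still open at least eight months in. If fieldwork stopped on the stated date, late enrolees would have no endline haemoglobin, or one taken before 12 months. Under {20c}, women without the measurement leave the primary analysis. Who leaves would depend on enrolment date and gestation at entry, and this loss would come on top of the 20% already allowed for ordinary attrition.

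The second is the definition. The primary outcome is fixed at one time point but collected over a three-month window that ends at that time point. Taken literally, nearly every measurement would precede the stated time, by up to three months.

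**Working it through.** **Inputs from the article.** Recruitment start 1 July 2022; stated end 30 June 2024; entry from 12 weeks; outcome at 12 months; endline visit at 9–12 months; final analysis at month 36; registration 3 March 2023; publication 9 August 2023; target 3240 women.

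**Assumptions.** Delivery at 40 weeks; 12 months = 365 days; 9 months = 274 days; one month = 30.44 days. Counting 12 months by calendar date moves the 12-month limits one day earlier. The first participant is taken to have entered on 1 July 2022.

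**1. Stated span.** 1 July 2022 to 30 June 2024 = 24.0 months. Month 36 is about 1 July 2025, which is 12 months after the stated end.

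**2. Time needed by a 12-week enrolee.** 40 − 12 = 28 weeks = 196 days = 6.44 months to delivery. Adding 9 gives 15.4 months; adding 12 gives 18.4 months.

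**3. Latest enrolment that fits the stated end.** Latest delivery = 30 June 2024 minus follow-up: about 1 July 2023 for 12 months and 30 September 2023 for 9 months. Latest enrolment = latest delivery − 7 × (40 − gestation at entry) days.

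| Gestation at entry | For a 12-month measurement | For a 9-month visit |
|---|---|---|
| 12 weeks | 17 December 2022 | 18 March 2023 |
| 20 weeks | 11 February 2023 | 13 May 2023 |
| 28 weeks | 8 April 2023 | 8 July 2023 |

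**4. Women entering while recruitment was known to be open.**

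- *3 March 2023.* Delivery by 1 July 2023 is 120 days away, or 17.1 weeks, and 40 − 17.1 = 22.9. Women below about 23 weeks miss 12 months. A 12-week enrolee delivers about 15 September 2023 and reaches 9 months about 15 June 2024, so all can reach 9 months.
- *9 August 2023.* Delivery on that very day gives 12 months on 8 August 2024, so no new enrolee reaches 12 months by the stated end. For 9 months, delivery by 30 September 2023 is 52 days away, or 7.4 weeks, and 40 − 7.4 = 32.6. Only women at about 33 weeks or later fit. A 12-week enrolee reaches 9 months about 21 November 2024 and 12 months about 20 February 2025.

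**5. Sensitivity to delivery at 37 weeks.** The thresholds move by three weeks, to about 20 weeks for 12 months on 3 March and about 30 weeks for 9 months on 9 August. The 12-month result for 9 August does not change.

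**6. Room before month 36.** A 12-month visit by 1 July 2025 requires delivery by about 1 July 2024, and so 12-week enrolment by about mid-December 2023. This leaves no time for database lock; each month reserved for lock moves that limit one month earlier.

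**7. Time point.** The Primary outcome section and Table 1 say 12 months. Section {13}, the Table 2 footnote and section {18a} say 9–12 months. No sentence links the two.

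The sample size is unaffected: 86 / 0.80 = 107.5, rounded up to 108, and 108 × 30 = 3240, as stated.

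**The case against.** The end date is an anticipated date in a status paragraph. Nothing says follow-up will be cut off then, and the month-36 analysis suggests a longer plan, so the date may be a clerical outlier. This stands in part: no loss of data has been shown, only that it would follow if the date were kept. But the date is the only trial end the article gives, and it cannot be met together with the article's own outcome for women then being recruited.

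A reader might infer several stronger things that the article does not support.

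- *That the month-24 end and the month-36 analysis contradict each other.* Analysis after trial end and database lock is normal. A 12-month gap is long and unexplained, but possible.
- *That 3240 women would have to be recruited in about 5.5 months, or 590 a month (3240 / 5.5).* That is the extreme case, in which every woman enters at exactly 12 weeks and is seen at exactly 12 months. With a 9-month visit, entry at 20 weeks allows 10.4 months (about 310 a month) and entry at 28 weeks allows 12.2 months (about 265 a month).
- *That measurement time will differ between arms.* Outcome assessors are unblinded and no target date within the window is given, so it could. But section {18a} sets the same occasions at intervention and control sites, and the visit intervals follow the infant immunisation schedule. Nothing indicates that scheduling differs by arm.

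How the analysis should treat visits outside the window, or adjust for time since birth, can be left to the analysis plan. The time point of the primary outcome cannot, because the protocol itself states it in two ways.

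**Conclusion.** The point holds. The stated end allows a 12-month measurement only for women enrolled by about mid-December 2022 (12 weeks) to early April 2023 (28 weeks). It allows a 9-month visit only for those enrolled by about mid-March to early July 2023. Recruitment was still open at an undated point between 3 March and 9 August 2023. At both ends of that range some or all new enrolees miss 12 months. Whether any miss the 9-month bound depends on where in the range the status statement falls: none at the start, and all below about 33 weeks at the end.

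The month-36 analysis date sits 12 months later without explanation, and it is the date that leaves room for full follow-up. The mismatch between a 12-month outcome and a 9–12 month visit is a separate inconsistency and does not depend on any calendar assumption. The calendar results rest on delivery at 40 weeks; delivery at 37 weeks moves them by three weeks and does not alter the conclusion.

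**What to change.** 1. Restate the trial end as the last participant's endline visit. Give a recruitment closing date about 18.4 months or more before that visit, which covers a woman entering at 12 weeks and seen at 12 months. Leave enough time for database lock between the last visit and the month-36 analysis. Placing the last visit at month 36 itself would leave none.
2. Reconcile the Primary outcome section and Table 1 with {13}, Table 2 and {18a}. Define the primary outcome as haemoglobin measured by the study team at the final visit, with one stated window and one target date for both arms.
3. Report months since birth at measurement by arm, so that any difference in timing can be seen.

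The cost is wording in the protocol and the registry entry, plus one descriptive table. The longer follow-up is already implied by the month-36 analysis date. If fieldwork is in fact resourced only to 30 June 2024, which the article does not say, the recruitment closing date becomes a real constraint and has to be settled first.

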## Data Availability

The Principal Investigator, project manager, database manager and study statistician will have access to the final study dataset. The study team maintain the right to exclusive use of the data until the primary analysis is published or for 24 months after the end of the trial (whichever comes sooner). After this time, the data will be made publicly accessible as per the University of Oxford Open Access policy.

## Abbreviations

AE: Adverse event
AMB: Anemia Mukt Bharat: the Government of India programme for anaemia
ANM: Auxiliary nurse midwife
ASHA: Accredited Social Health Activist
CRF: Case record form
EQ5D: Euro-Quol Quality of Life measure - five domains
ERIC: Expert recommendations for implementing change
EUC: Enhanced usual care
FGD: Focus group discussion
FIGO: International Federation of Gynaecology and Obstetrics
GAD7: Generalised Anxiety and depression scale
GDM: Gestational diabetes mellitus
GCP: Good Clinical Practice for research
HbA1c: Glycated haemoglobin
HDP: Hypertensive disorder of pregnancy as per ISSHP 2018 guidelines
ICC: Intracluster correlation coefficient
ISSHP: International Society for the Study of Hypertension in Pregnancy
LMUP: London Measure of Unplanned Pregnancy
MRC: Medical Research Council, UK
NCD: Non-communicable diseases
NFHS: National Family Health Survey of India
OGTT: Oral glucose tolerance test
PHC: Primary Health Centre
PHQ9: Patient Health Questionnaire
SAE: Severe adverse event
SHP: SMARThealth Pregnancy
UKRI: United Kingdom Research and Innovation
